##### **3.2.2 Secondary efficacy outcome measures**

- 3.2.2.1 The secondary aim of identifying genes correlated with nutritional supplementation with lycopene or fish oil will be accomplished by analyzing gene expression of 30,000 human genes using a cDNA array. Identification of a gene cluster associated with lycopene or fish oil but not placebo will be

accomplished using hierarchical clustering[62], or alternate algorithms that use permutation t-test statistics to account for the multiplicity of tests accomplished using such large scale microarrays[63]. If sufficient nucleic acid samples remain after primary outcome measure assessment, and microarray analysis, confirmatory Taqman quantitative polymerase chain reactions will be used to confirm the specific induction of genes identified in these studies by lycopene or fish oil.

- 3.2.2.2 To accomplish the secondary aim of identifying genes correlated with baseline dietary intake, patients will be stratified for high and low intake of total energy, fat/meat/animal products, dairy/calcium, fish, vegetables, tomatoes/lycopene, vitamin E, and selenium as defined by the Willett Semi-quantitative Food Questionnaire. Separate microarray data analyses will be performed for each dietary factor by placing all patients with low intake ( $\leq$  median) into the first half of the data table, and subsequently all patients with high intake ( $>$  median). The same standard microarray hierarchical clustering and permutation t-test approaches as in 3.2.2.1 will then be used to identify genes whose expression differs between these groups.
- 3.2.2.3 We acknowledge that the study is underpowered to assess effects of nutrition supplementation on progression rates, given the heterogeneous nature of prostate adenocarcinoma. Nevertheless, it is compelling to perform exploratory data analysis to examine whether exploratory analysis may detect genes correlated with progression or lack of progression at 12 months in the MENS study. If any correlates are detected, they will be used to formulate a hypothesis for testing in further large scale studies, such as the multi-institutional CALBG or SWOG watchful waiting trials.
- 3.2.2.4 With watchful waiting, approximately 25% of patients will experience disease progression when assessed 12 months after study entry. To assess whether the

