We will select particular genes whose expression is correlated with baseline dietary intake for validation of activity of the supplement by an independent assay technique. Quantitative PCR accomplished with the Taqman technology[74-76] is ideally suited to target validation for the MENS study, since the RNA amounts available from clinical core needle biopsies range from 100-600 nanograms. These small amounts of RNA preclude the use of other techniques such as

Northern blot analysis, and are more easily modified for high throughput analysis of several gene targets as compared to RNase protection – RNase protection experiments are also cumbersome due to requirements for radioisotope use. The UCSF Comprehensive Cancer Center has a genomics core available to [name] laboratory which will carry out Taqman quantitative PCR[74-76]

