For the secondary specific aims (aims 1.2 through 1.4 defined above), we will consider a microarray dataset with measurements for 30,000 genes. For this exploratory investigation genes will be treated as being independent so as to first identify all possible genes that may indicate an effect due to the nutritional supplement (Aim 1.2) or to other dietary components (each considered as a binomial variable) (Aim 1.3). Fisher's exact test will be used to determine which genes result in differences in proportions with up or down regulated genes between groups. No adjustment for multiple comparisons will be made. Also, after all patients have had the potential to be followed for at least one year, they will be classified as to whether they had experienced disease progression within 1 year from protocol entry. The same exploratory techniques described above first using the baseline gene expression profile will be carried out to identify genes that may be associated with disease progression (Aim 1.4). Even though any nutritional supplement will be stopped at 3 months from the start of protocol therapy and the duration of any effect is unknown, this analysis will be repeated using the 3-month gene expression profile to identify the effects of any gene that might have been modified by protocol treatment. To account for genes with highly variable expression regardless of study arm, genes whose expression levels change two-fold in more than 20% of men on placebo (comparing three-month to baseline) will

be excluded from subsequent consideration. This might exclude possible predictors of outcome, but if there is variability within the placebo group then the results may be biased. This refining process will isolate potential predictors of nutritional change when assessing the primary as well as the secondary outcomes. Standard microarray gene expression software algorithms will facilitate analyses to determine if there are individual genes or clusters of genes associated with either supplement, dietary component or disease progression[62, 63] . Fisher's exact test will be used to determine which genes result in statistically significant differences between the groups.

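### Taqman on leftover RNA from the same men can verify the array reading, but cannot confirm that lycopene or fish oil induced the gene

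*Protocol*

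**What the plan says.** Protocol section 3.2.2.1 pursues the supplement-gene aim (Aim 1.2) by "analyzing gene expression of 30,000 human genes using a cDNA array". Genes linked to lycopene or fish oil but not to placebo are sought by clustering or by algorithms that "use permutation t-test statistics to account for the multiplicity of tests accomplished using such large scale microarrays".

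A second step follows, with a condition: "If sufficient nucleic acid samples remain after primary outcome measure assessment, and microarray analysis". If it is met, Taqman assays "will be used to confirm the specific induction of genes identified in these studies by lycopene or fish oil". No hold-out group or second cohort is named, and no rule says what counts as confirmed.

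Section 13 treats the array work as exploratory. It states that "Fisher's exact test will be used to determine which genes result in differences in proportions with up or down regulated genes between groups" and that "No adjustment for multiple comparisons will be made". Section 3.2.2.3 handles progression genes differently: any correlates found there only generate hypotheses, to be tested in larger studies elsewhere.

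**The concern.** Nucleic acid that remains after the primary assay and the arrays can only be that of the men who supplied the array data. Suppose a gene is unaffected by the supplement, but men in one arm happened to have larger spontaneous changes between their two biopsies. That imbalance is really present in their RNA. The array picks the gene because of it, and an accurate PCR finds it again. The better the two assays agree, the more such genes repeat.

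The re-assay therefore asks whether the array read the RNA correctly. The protocol's stated conclusion is about cause. This is separate from multiplicity: even with a permutation method, any false gene that survives is re-tested on the data that selected it. At stake is what Aim 1.2 may conclude, because its output is meant to steer further work on these pathways.

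**Working it through.** **Figures in the plan.** The protocol gives no figure for this step. The only relevant input is 29 evaluable men per arm (section 13). That holds up: Fisher's exact test at one-sided 0.025, 20% v 60%, 29 per arm has 83.0% power against the stated 81%, and 87/0.9 = 96.7, rounded up to 97. The point below does not affect it.

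**Inputs.** 30,000 genes (section 3.2.2.1); 29 v 29 (section 13); two-fold change in at most 20% of placebo men (the section 13 variability filter). *Assumed:* ρ, the per-man correlation between array and PCR log changes, at 0.5, 0.7 and 0.9; PCR pass rule p<0.05 in the same direction; array cut p<0.05 or p<0.001. The protocol gives none of these.

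**A. Continuous scale (t-tests), no supplement effect.** If each assay reads a shared true change plus its own error, the two arm differences are also correlated at ρ. The chance that a null gene selected at z repeats on PCR is

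P(Z₂>1.96 | Z₁>z) = ∫ from z to ∞ of φ(x)·Φ((ρx−1.96)/√(1−ρ²)) dx ÷ (1−Φ(z)).

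| Selection | ρ=0.5 | ρ=0.7 | ρ=0.9 | Separate men |
|---|---|---|---|---|
| z=1.96 (two-sided p<0.05) | 18% | 33% | 59% | 2.5% |
| z=3.09 (one-sided p<0.001) | 38% | 70% | 99% | 2.5% |

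Simulated t-tests at 29 v 29 with two-sided cuts agree: 18%, 32% and 59% at p<0.05; about 37–39%, 74% and 99% at p<0.001. If all genes were null, p<0.001 would select 30,000 × 0.001 = 30 genes per comparison.

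**B. Fisher's test on two-fold change (section 13).** One direction, one supplement against placebo, one-sided 0.025, 29 per arm, exact null hit rates:

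- Two-fold rate 10% in both arms: 0.00433 × 30,000 = 130 null hits.
- Two-fold rate 20% in both arms: 0.01059 × 30,000 = 318 null hits.

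Share of those null hits significant again on PCR (300,000 simulated null genes per setting):

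| Two-fold rate | ρ=0.5 | ρ=0.7 | ρ=0.9 | Separate men |
|---|---|---|---|---|
| 10% | 2.4% | 6% | 17% | 0.4% |
| 20% | 5.5% | 11% | 24% | 1.1% |

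In counts, if all genes were null: at a 10% rate, 130 × 2.4% ≈ 3 to 130 × 17% ≈ 22 repeat, against 130 × 0.43% ≈ 0.6 in separate men. At 20%, 318 × 5.5% ≈ 17 to 318 × 24% ≈ 76 repeat, against 318 × 1.06% ≈ 3.4.

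**C. Pass rule.** If confirmed meant only the same direction, 69–73% (ρ=0.5) to 98–99% (ρ=0.9) of null Fisher hits would pass.

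**D. Does the step discriminate?** Yes, in part. A real effect of the primary endpoint's size (20% v 60%) that is picked by the array at p<0.05 passes PCR 98–99% of the time, against 18–59% for null genes.

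**The case against.** The strongest reply is that this is a platform check on candidates. Aim 1.2 looks for leads for later research, section 13 calls the array work exploratory, the step depends on leftover RNA, and the pass rule may sit in an analysis plan that is not shown. Much of that stands, and it limits the weight of the point. It does not rescue the sentence, because the protocol itself fixes both the material and the causal conclusion.

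Four stronger readings are tempting and are not supported:

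- *That the step cannot tell real from false hits.* It can, in part. At array p<0.05 it removes 82%, 68% and 41% of null genes (100% minus 18%, 32% and 59%). Discrimination is nearly lost only with a strict array cut and very high assay agreement.
- *That one pass rate can be quoted.* Results depend on ρ, the cut and the test. Section 13's Fisher test gives much lower shares than t-tests.
- *That genes will be published with a PCR-confirmed label, p values and effect sizes.* The protocol does not say so.
- *That section 8.2 makes the same error.* It says Taqman "is ideally suited to target validation for the MENS study", but the genes there are picked on baseline dietary intake, not on the contrast between randomised arms.

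**Conclusion.** The point holds in limited form. The re-assay described in section 3.2.2.1 can remove array measurement error, but it cannot establish induction by lycopene or fish oil, because the men and RNA that selected the genes are used again. Under the assumed correlations of 0.5 to 0.9, false genes repeat far more often than they would in separate men: roughly 7 to 40 times as often with t-tests (18/2.5 to 99/2.5), and about 5 to 40 times with section 13's Fisher test (5.5/1.1 to 17/0.4).

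The number of chance hits that reach the step depends on which multiplicity statement governs. Section 13 makes no adjustment; the permutation option in section 3.2.2.1 would leave fewer. The non-independence remains either way. The matter is minor: no primary analysis, sample size or patient is affected.

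**What to change.** Amend section 3.2.2.1 so that Taqman on RNA from the men who supplied the array data is reported as technical (assay) verification only. State that its p values and effect sizes are not presented as evidence of supplement induction. Keep the genes as candidates and reserve confirmation for separate men in a later study, as section 3.2.2.3 already does for progression genes. This is a wording change and needs no extra men, biopsies or assays.

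Splitting the trial into discovery and test parts is not recommended. With two thirds for discovery (about 19 v 19) and one third for testing (about 10 v 10), power to pick up a primary-sized effect at array p<0.001 falls from 75% to 43%. The test stage, with Bonferroni over 30 genes, has about 15% power by t-test and 3% by two-sided Fisher. That would defeat an aim meant to find candidates.

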## 1. Objectives

- 1.1 Primary: To measure gene expression in normal prostate tissue acquired by needle biopsy in men assigned to placebo, lycopene or fish oil nutritional supplements at baseline and after intervention. The primary outcome measure is a two-fold decrease in mRNA transcript level. The primary study endpoint is the difference in the proportion of the patients in a nutritional supplement arm compared to a placebo control arm achieving a two-fold decrease in the gene of interest. Quantitative polymerase chain reaction will assess modulation of expression of the *insulin-like growth factor 1 (IGF1)* and the cyclooxygenase 2 (*Cox-2*) gene in lycopene and fish oil recipients respectively.
- 1.2 Secondary: We will use cDNA microarrays with 30,000 independent clones to identify new candidate molecular targets for lycopene and omega-3 response pathways deserving further study.
- 1.3 Secondary: To correlate baseline gene expression patterns determined by cDNA array analysis with self-reported dietary intake. Based on previous epidemiologic, *in vitro*, and *in vivo* studies, we hypothesize that higher intake of total energy, fat/meat/animal products, dairy/calcium, and lower intakes of fish, vegetables, tomatoes/lycopene, vitamin E, and selenium will be associated with particular gene expression profiles.
- 1.4 Secondary: We will assess if there are gene expression patterns correlated with progression or lack of progression as assessed at a time point 12 months after study entry.
- 1.5 Secondary: We will assess if lycopene or omega-3 supplements affect the incidence of tumor progression.

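### Aim 1.3 tests each dietary factor without allowing for total energy, so its gene lists cannot separate a food or nutrient from how much a man eats

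*Protocol*

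**What the plan says.** Objective 1.3 hypothesises that "higher intake of total energy, fat/meat/animal products, dairy/calcium, and lower intakes of fish, vegetables, tomatoes/lycopene, vitamin E, and selenium will be associated" with particular expression profiles. Total energy is thus named as something expected to relate to expression, in the same list as the foods and nutrients.

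Section 3.2.2.2 states the method: "patients will be stratified for high and low intake of total energy, fat/meat/animal products, dairy/calcium, fish, vegetables, tomatoes/lycopene, vitamin E, and selenium", with intake "as defined by the Willett Semi-quantitative Food Questionnaire". The groups are at or below the median and above it. "Separate microarray data analyses will be performed for each dietary factor by placing all patients with low intake" in one group and the remaining men in the other, using hierarchical clustering and permutation t-tests.

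Section 13 gives the same structure for this aim, with dietary components "each considered as a binomial variable" and Fisher's exact test between groups. Section 8.2 (baseline molecular assessment) speaks of intake quartiles instead of a median split. The point here does not depend on where the cut falls.

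No energy density, energy residual, stratification by energy or multivariable model appears for Aim 1.3. The only stratified adjustment named is Mantel-Haenszel in section 13. It is for the primary aim, if needed, and the surrounding text on confounding concerns balance between the randomised arms.

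**The concern.** Aim 1.3 compares men by the diet they chose, so randomisation gives it no protection. If a man who eats more also eats more of a given food, a split on that food partly sorts men by total energy. Should energy relate to expression, as the aim itself expects, energy confounds the comparison. Two things can follow.

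- **Spill-over.** A gene tied only to energy appears on the list of a food or nutrient that has nothing to do with it.
- **Masking.** The hypothesis runs in opposite directions: higher energy, but "and lower intakes of fish, vegetables, tomatoes/lycopene, vitamin E, and selenium will be associated with particular gene expression profiles". If those intakes rise with energy, the two effects pull against each other within the unadjusted split, and the hypothesised pattern can vanish.

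The lists also have a use. Section 8.2 takes selected diet-correlated genes on to quantitative PCR to validate supplement activity, from core biopsies that yield 100 to 600 ng of RNA. Energy-driven genes listed under tomato or fish would use some of that material.

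**Working it through.** The protocol states no figure for Aim 1.3, so there is none to reproduce. The calculation below is illustrative, and **every correlation in it is an assumption**.

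**Inputs from the protocol.** Eight factors, seven of them other than energy; one-at-a-time median splits (3.2.2.2); 97 men accrued and 87 evaluable (4.4 and 13).

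**Model.** Energy E and diet composition C are independent standard normals. Intake of a factor is F = ρE + √(1−ρ²)·C. Expression is G = aE + cC + noise, with variance 1. Then

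corr(F, G) = aρ + c√(1−ρ²).

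The test is a two-sided 5% t-test of G between the halves of F, standing in for the permutation t-test. Fisher's exact test on dichotomised expression was not simulated. It uses the same groups, so it meets the same confounding. The adjusted version splits the residual of F regressed on E.

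**1. How far the two splits coincide.** For bivariate normal intakes the agreement of the median splits is 0.5 + arcsin(ρ)/π: 50% at ρ=0, 56% at 0.2, 63% at 0.4, 71% at 0.6 and 80% at 0.8.

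**2. Spill-over (c=0, so the nutrient has no effect of its own), n=97.** Here corr(F, G) = aρ. A median split multiplies the correlation by √(2/π) = 0.798, and t is about r√95/√(1−r²), where r is the reduced correlation.

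| ρ | a | aρ | r | expected t | flagged, approx. | flagged after adjustment (simulated) |
|---|---|---|---|---|---|---|
| 0.3 | 0.2 | 0.06 | 0.048 | 0.47 | 7% | 3–5% |
| 0.5 | 0.3 | 0.15 | 0.120 | 1.18 | 21% | 3–5% |
| 0.7 | 0.3 | 0.21 | 0.168 | 1.66 | 37% | 3–5% |
| 0.8 | 0.4 | 0.32 | 0.255 | 2.57 | 72% | 3–5% |

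Simulation gives about 8% at the weak end and 74% at the strong end, within about two points of the approximation. At n=87 the simulated rates are about 7%, 19%, 35% and 67%. For a factor weakly tied to energy the effect is small: at ρ=0.2 and a=0.3 (n=87) the rate is 7%.

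**3. Masking (a=+0.3, c=−0.35), n=97.** This is the direction in Objective 1.3 for fish, vegetables, tomatoes, vitamin E and selenium.

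- ρ=0.3: corr = 0.090 − 0.334 = −0.244; power about 46%.
- ρ=0.5: corr = 0.150 − 0.303 = −0.153; power about 23%.
- ρ=0.7: corr = 0.210 − 0.250 = −0.040; power about 7%.

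With the energy residual, power is about 80% in each case.

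**4. The opposite model: G depends on the amount eaten, F, with correlation 0.35, n=97.** The unadjusted split has about 80% power throughout. The residual split sees only 0.35√(1−ρ²), which is 0.334, 0.303, 0.250 and 0.210 at ρ = 0.3, 0.5, 0.7 and 0.8. Its power is 75%, 67%, 49% and 36%.

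**The case against.** The strongest reply is that amount eaten is a defensible exposure. The supplements are fixed daily amounts, the tomato and fish strata are servings per week, and the diet-associated genes are meant to bear on supplement activity. Residual adjustment changes the question from amount to composition, and step 4 shows what that costs if amount is what matters. This stands. It rules out replacing the planned analysis, but it does not rule out adding to it.

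A reader might also infer more than the protocol supports:

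- **That the plan fixes absolute intake.** This is the natural reading, but the protocol refers only to intake as the questionnaire defines it. A separate analysis plan could derive the variable differently. What the protocol does fix, in two sections, is separate two-group comparisons with energy as a parallel factor.
- **That genes will be reported as specific to fat, dairy, vegetables or vitamins.** The text promises exploratory correlations and associations, not factor-specific effects.
- **That all the factors suffer alike.** At most seven are affected, and only as far as each tracks energy. The protocol says more than half of eligible men already took nutrition supplements (5.3), so vitamin intake need not follow energy if supplements are counted.

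Energy does get its own gene list, so overlap with the other lists could be seen. However, no comparison of lists is planned, and overlap cannot recover an association that was masked. With 30,000 genes and no multiplicity adjustment, a nominal 5% test already gives about 0.05 × 30,000 = 1,500 chance calls per factor if no gene is truly related. How much spill-over adds depends on how many genes relate to energy, which is unknown.

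**Conclusion.** The concern holds in a limited form. As planned, the Aim 1.3 gene list for any non-energy factor that rises with energy cannot tell that factor from total intake. Where the hypothesised directions oppose each other, real associations can be hidden. The size rests entirely on assumed correlations: about 8% to 74% false attribution over the range tried (n=97), against 3% to 5% after adjustment, with little effect for factors weakly tied to energy. It does not follow that the aim is unanswerable or that the unadjusted split is wrong in itself, since that split has more power if the effect comes from the amount eaten. Priority is low: one exploratory secondary aim is affected, and the randomised comparison and primary endpoint are not.

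**What to change.** In sections 3.2.2.2 and 13, for the seven non-energy factors, add an energy-adjusted analysis beside the planned unadjusted split. Regress intake on total energy from the same baseline questionnaire, take the residual and group men at its median. Analyse total energy as recorded. State that a gene will be described as related to a particular food or nutrient, rather than to total intake, only if the association holds after energy adjustment.

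The cost is one regression per factor on data already collected and a second set of exploratory gene lists to report. The adjusted analysis loses power if amount, not composition, drives expression, which is why the unadjusted analysis is kept.

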### **Safety outcome measures**

As the agents proposed for study here are widely used without report of adverse effects, and since in clinical studies reported to date there were no adverse effects noted, we do not anticipate that lycopene or fish oil supplementation will adversely affect prostate cancer progression.

## **4 Subjects**

### **4.1 Who and why**

As described in the Background section (2.5) above, many men with favorable-risk prostate cancer may expect extended survival without definitive therapy. There is a need for interventions in these patients that may delay or prevent disease progression with a minimal impact on health-related quality of life (HRQOL). A large proportion of prostate cancer patients use nutritional supplements and other “complementary” treatments toward this end, but few of these treatments have been formally evaluated. A growing number of studies confirm that low-risk clinical and pathologic risk characteristics consistently predict tumors with relatively low short-term metastatic potential, and that close monitoring can identify early those patients opting for deferred intervention who show signs of a higher progression risk. These patients are the target cohort for our study. Patients at risk for prostate cancer seen in the Urologic Oncology Program at the University of California at San Francisco at UCSF/Mt. Zion are potential subjects for this study.

After the 3-month intervention, patients will return to the care of their referring UCSF urologist for subsequent 21 months of follow-up in the MENS study, following which the standard of care is for follow-up at intervals no greater than every six months.

